### Statistical analysis

#### Safety run-in period

Although Bactek has previously been used in preterm-born infants, we included a formalised safety run-in period as follows:

Recruit and randomise the first four infants with the expectation that half of these participants would be allocated the active arm. The IDMC reviews the allocation and advises if more participants need to be recruited.Administer the study product as per protocol and monitor randomised infants for 1 week post-randomisation, ideally while still in hospital.Record any adverse events. If no adverse events are reported, write an email to the IDMC Chair declaring this.If there are adverse events, generate a safety report for IDMC and hold open and closed meetings to discuss the progression of the study.Decisions which the IDMC could make following the end of the safety run-in period:Do not proceed with any further recruitment according to the current protocol and indefinitely pause the trial. This would be due to adverse events being reported which were deemed to be serious (defined as any untoward medical occurrence(s) that results in death, hospitalisation or prolongation of existing hospitalisation, persistent or significant disability/incapacity) and probably/definitely related to the study product. We would liaise with the local site study teams and manufacturer to determine the best way to resolve any issues that are identified.IDMC to meet at 3 months to review safety on a greater number of participants. This would be due to either non-serious adverse events occurring which were probably or definitely related to study product or serious adverse events occurring which were possibly related to study product. Recruitment would continue during this period unless major safety concerns were identified by the TMG.Continue recruitment for the rest of the internal pilot. This would be due to no adverse events occurring (confirmed via email to IDMC), non-serious adverse events which were at most possibly related, or serious adverse events which were at most unlikely related to the study product.IDMC writes a letter of recommendation to the TSC who in turn will write to the funder at the end of the safety run-in period.

During March to May 2025, four infants were recruited. There were no adverse events reported to the study team, which after assessment by the IDMC Chair, resulted in a decision by the TSC to commence full recruitment from June 2025.

### Interim analysis

At the interim analysis stage, we will compare the proportion of infants experiencing at least one health professional diagnosed LRTI within 6 months between trial arms by fitting a two-level Poisson (or negative binomial/logistic) regression model, with multiple infants nested within mothers and robust standard errors. Models will also adjust for gestational age and anti-RSV prophylaxis (as per randomisation factors). Results will be reported to our IDMC as adjusted risk differences (using the margins command in Stata), 95% CIs and p values. As per our design parameters, should our one-sided p value be >0.43, this would provide statistical indication of a lack of benefit of our intervention. Additional data (eg, other outcomes, including safety data) may be considered by our IDMC when deciding whether to progress or stop at this stage.

### Analysis of primary outcome

Analysis will be performed based on intention to treat. Our primary analysis will compare the proportion of participants receiving a health professional diagnosed LRTI post-randomisation between 37 and 43 weeks PMA or discharge if earlier and 1-year corrected age between arms by fitting a two-level Poisson (or negative binomial) regression model, with multiple births nested within mothers and robust SEs. Models will also adjust for gestational age and anti-RSV prophylaxis (as per randomisation factors). Results will be reported as risk ratios, 95% CIs and p values. Univariable, as well as adjusted models will be presented. Missing data are expected to be minimal but will be handled within a multiple imputation framework.

### Analysis of secondary outcome measures

Secondary outcomes will be analysed using appropriate regression models (eg, linear, Poisson, negative binomial, flexible parametric survival models), adjusting for stratification and minimisation variables as per the primary analysis.

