### Trial intervention

Bactek or placebo to match is packaged, labelled and QP released by Inmunotek (Madrid, Spain). St Mary’s Pharmaceutical Unit (SMPU, Cardiff and Vale University Health Board) (MIA (IMP) 359929) imports the IMP to the UK and provides final regulatory release. SMPU warehouses the IMP supply and distributes it to the study sites.

The dosing schedule of 2 sprays (each 0.1 mL) of IMP (300 Formazin Turbidity Units (FTU)) is being administered, once daily, from 37 to 43 weeks’ PMA or discharge if earlier up to 1 year of corrected age. A video showing how to administer the IMP is shown on the BALLOON website. All data thus far collected, including infants, preschool aged children and adults, support using the same dose of 2 daily sprays of 300 FTU.^812 19^,^21^

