### Outcomes

#### Primary outcomes

The primary outcome is the presence/absence of parent-reported, health professional-confirmed unscheduled visits for LRTIs to GPs, A&Es, paediatric assessment units or hospital admissions between 37 and 43 weeks’ PMA (or discharge if earlier) and 1-year corrected age, compared between the two treatment arms.

An LRTI is defined as:

Fever (≥38°C) or a runny nose (rhinitis) for at least 12 hours, plus one additional symptom from the following:moist coughwheezingshortness of breathtachypnoeaintercostal recessionpoor feeding

Secondary outcomes include:

The actual number of parent-reported, health professional-confirmed unscheduled visits for LRTIs to GPs, A&Es, paediatric assessment units and hospital admissions between 37 weeks’ PMA (or discharge if earlier) and 1-year corrected age. The LRTI will be considered to be a new episode if there is an intervening period of at least 72 hours between episodes when the infant is well.The time to first parent-reported, health professional-confirmed unscheduled visit for LRTI to GPs, A&Es, paediatric assessment units and hospital admissions between 37 and 43 weeks’ PMA (or discharge if earlier) and 1-year corrected age.Parent-reported wheeze episode between 37 and 43 weeks’ PMA or discharge if earlier and 1-year corrected age.A wheeze episode is defined as an episode of wheezing that lasts at least 1 day with signs of increased work of breathing, such as shortness of breath, cough or chest retraction or with any combination of these additional symptoms. A WheezeScan device is provided to parent(s)/guardian(s) to detect and differentiate wheezing from other breath sounds.Identification of virus(es) associated with LRTIs.Parent-reported use of respiratory medications including bronchodilators, antibiotics and systemic corticosteroids.Somatic growth differences (weight, length and head circumference).Parent(s)/guardian(s) reported time missed from work and/or nursery time missed for the infant.Volume of adverse reactions.

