### Randomisation

Once eligibility has been confirmed and the parents/guardians have consented, randomisation to the intervention is performed. The randomisation list was prepared by an independent CTR statistician. Participants are being randomised 1:1 using minimisation with a random element (p=0.8). Allocations are minimised by gestational age and anti-RSV prophylaxis—both assumed to have a strong prognostic relationship with the primary outcome. Maternal vaccination against RSV was introduced in the UK during the winter of 2024. Although universal anti-RSV prophylaxis may be introduced in the winter of 2025 to replace existing targeted anti-RSV treatment, we already have incorporated plans to stratify the intervention based on receipt of any anti-RSV prophylaxis. To avoid any issues with inadvertent unblinding or dosing errors, multiple births are being randomised to the same arm. Allocation to Bactek or placebo is double blinded, the allocation is not known to clinicians, the infant’s family or the study team with the exception of the independent CTR statistician. The list was uploaded to a web-based randomisation system provided by the Centre for Healthcare Randomised Trials (CHaRT) (University of Aberdeen). A member of staff at the recruiting site performs randomisation on the web-based randomisation system which produces the pack ID that the infant is allocated to and a participant ID. The BALLOON IMP is then prescribed by an appropriately qualified individual. If necessary, unblinding can be performed on the web-based randomisation system by the PI.

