### Data collection and sampling

#### Clinical assessments

After documentation of eligibility and consent in the web-based randomisations system, subsequent data collection is in Research Electronic Data Capture (REDCap) by the recruiting site staff and parents/guardians complete an App provided by Your Research B.V. (Huizen, Netherlands) to record respiratory symptoms, non-respiratory symptoms and adherence to the IMP. A WheezeScan device is provided to all parent(s)/guardian(s) to detect and differentiate wheezing from other breath sounds. If respiratory symptoms are reported on the App, the recruiting site staff will be able to access the data including reporting of respiratory symptoms, as they will have access to the App dashboard to review data entries of all participants recruited from their site. They will then verify if an LRTI has occurred.

Initial data collection in REDCap focuses on maternal history, information about the family, antenatal information, details around the infant’s birth and neonatal admission. Monthly follow-up phone calls are being carried out by the site staff at 1, 2, 4, 5, 7, 8, 10 and 11 months of age focusing on adherence, concomitant medications and ensuring the parents have adequate BALLOON IMP and swabs for the next month and all LRTIs have been verified. Face-to-face visits either at the infant’s home or in hospital take place at 3, 6, 9 and 12 months of age. The face-to-face visits focus on IMP adherence, receipt of concomitant medications, supply of new IMP sprays and weighing the returned sprays (to further aid adherence), ensuring all LRTIs have been verified, and completing ongoing medical history including any potential adverse events.

Infants remain in follow-up for safety until 13 months’ corrected age.

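### The covariate rule for all secondary outcomes, as written, leaves the infant's starting size and sex out of the growth models and so gives up precision

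*Protocol article*

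**What the plan says.** The section Analysis of secondary outcome measures is a single sentence covering all secondary outcomes. On model type it says: "Secondary outcomes will be analysed using appropriate regression models (eg, linear, Poisson, negative binomial, flexible parametric survival models". On covariates it says: "adjusting for stratification and minimisation variables as per the primary analysis".

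Two other sections identify those covariates. Randomisation states: "Allocations are minimised by gestational age and anti-RSV prophylaxis". Analysis of primary outcome states: "Models will also adjust for gestational age and anti-RSV prophylaxis (as per randomisation factors". Neither names size or sex.

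Growth is in the list of secondary outcomes as "Somatic growth differences (weight, length and head circumference". No scale (raw, standardised or change) and no visit is given.

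On baseline data, Clinical assessments says: "Initial data collection in REDCap focuses on maternal history, information about the family, antenatal information, details around the infant’s birth and neonatal admission". Neither sex nor size at enrolment is named there.

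**The concern.** The primary outcome is whether an infant had an LRTI visit. It has no baseline value, so adjusting for the two minimisation factors is reasonable. Growth differs: an infant's size at the start, and sex, can both be expected to predict size a year later. Carrying the primary covariate set over to growth leaves that variation in the residual.

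What is at stake is the width of the confidence intervals for weight, length and head circumference. Wider intervals than necessary make it easier to miss a modest difference in growth, in either direction, after up to a year of daily dosing. Because allocation is random, leaving these covariates out does not bias the estimate.

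**Working it through.** **The plan's own figure.** The trial is sized on LRTI, 55% against 40%, with one-sided alpha 0.025 and 90% overall power. With pooled variance under the null:

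n per arm = [1.960 × √(2 × 0.475 × 0.525) + 1.282 × √(0.55 × 0.45 + 0.40 × 0.60)]² / 0.15² = 230.8, so 231 per arm and 462 in total, against 460 stated. Then 460 / 0.85 = 541.2, so 542, as stated. The figure of 460 analysable infants (230 per arm) is therefore a sound input. The article states no target for growth.

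**Inputs for growth.**
- From the article: 460 analysable infants, allocated 1:1.
- Conventional: two-sided 5% level, and 80% power as a reference point.
- Assumed: r, the correlation between starting and final size that remains after gestational age and prophylaxis are in the model. The documents give no value, so 0.2 to 0.7 is shown. SD below means the residual SD under the stated covariates.
- Sibling clustering is ignored throughout.

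**Without starting size.** SE = √(2/230) = 0.0933 SD. Detectable difference at 80% power = (1.960 + 0.842) × 0.0933 = 0.261 SD.

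**With starting size as a covariate.** The residual variance is multiplied by 1 − r² and the SE by √(1 − r²). Power for the same 0.261 SD is Φ(2.802/√(1 − r²) − 1.960). The equivalent number of infants is 460/(1 − r²).

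| r (assumed) | Variance factor | SE reduction | Detectable difference, 80% power | Power for 0.261 SD | Equivalent infants |
|---|---|---|---|---|---|
| none | 1.00 | – | 0.261 SD | 80% | 460 |
| 0.2 | 0.96 | 2% | 0.256 SD | 82% | 479 |
| 0.3 | 0.91 | 5% | 0.249 SD | 84% | 505 |
| 0.5 | 0.75 | 13% | 0.226 SD | 90% | 613 |
| 0.7 | 0.51 | 29% | 0.187 SD | 97.5% | 902 |

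**Sex.** If boys and girls differ by d within-sex SDs (assumed, 0.4 to 0.8) and are equally frequent, sex explains (d²/4)/(1 + d²/4) of the variance: 0.04/1.04 = 4% at d = 0.4 and 0.16/1.16 = 14% at d = 0.8. Taking r = 0.5 with sex at 8%, and treating the two as additive, the SE falls by 1 − √(1 − 0.25 − 0.083) = 18%. Additivity is generous, because starting size already carries part of the sex difference.

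**The case against.** The strongest reply is that the sentence is generic. It sets a common minimum for outcomes of several kinds, does not bar further covariates, and the analysis plan that would add them is not shown. This stands in part: the analysis plan may already include baseline size. But the article is not silent on covariates. It states a rule and ties it to the primary analysis, and an analyst following that rule would omit starting size and sex.

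It is also fair that the gain depends on an unstated correlation. At r = 0.2 it is only about 2 percentage points of power. Gestational age is already in the model and may account for some of what starting size would explain, which is why r is defined above as the correlation remaining after it.

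The extra covariates are not certain to be at hand either. The article names neither sex nor enrolment size among the data collected, although it does record "details around the infant’s birth and neonatal admission".

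Two stronger readings are tempting and should not be made:
- A reader might infer that growth will be analysed as raw measurements. The article does not say so; the scale is unstated, and an article may leave that to the analysis plan.
- A reader might infer that the spread in starting age (treatment runs "from 37 to 43 weeks’ PMA or discharge if earlier up to 1 year of corrected age", so 43 − 37 = 6 weeks or more) adds noise to the result. Size at 1-year corrected age is measured at a common age, so the spread adds none to it. It would matter for a change from enrolment, which the article does not specify, and it is a reason to record age when an enrolment measurement serves as a covariate.

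**Conclusion.** The point holds as one of precision. Followed as written, the covariate rule gives growth models without starting size or sex. Over assumed residual correlations of 0.2 to 0.7, including starting size would lift power for a 0.26 SD difference from 80% by about 2 to 17 percentage points (10 points at 0.5). These figures assume 460 analysable infants and ignore sibling clustering, and the 80% starting point is a reference, not a target of the trial.

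There is no bias, and the primary analysis, sample size and interim rule are unaffected. This is a desirable improvement to one secondary outcome, not a flaw that threatens the trial.

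**What to change.** Add one sentence to the secondary-outcome rule, or confirm it in the analysis plan: for weight, length and head circumference at 1-year corrected age, the model also includes sex and the same measure at enrolment together with age at measurement, or the measure at birth if no enrolment value is held, in addition to gestational age and anti-RSV prophylaxis. Using z-scores standardised for corrected age and sex, for both outcome and baseline, achieves the same. Keep the nesting of infants within mothers.

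The cost is small: computing z-scores if they are used, checking that sex and a starting measurement are held, and stating how missing baseline values are handled (multiple imputation is already planned for the primary analysis). With 31 of 542 infants recruited when the article was written, this can be prespecified early.

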### Subgroup analyses

We will extend our primary analysis by fitting trial arm by subgroup interaction terms to explore any differential intervention effects by gestational age and anti-RSV prophylaxis.

### Current status of trial

Recruitment started in March 2025 and the safety run-in completed in June 2025. Since no reported adverse events were reported, the IDMC gave the go-ahead to start full recruitment in June 2025. At the time of writing (25 September 2025), 31 infants have been recruited, and twelve recruiting sites were open with 3–4 due to open in the next 2 months.

## Ethics and dissemination

The current version of the BALLOON Protocol is 1.4, dated 4 June 2025. Ethics permission has been granted by the Wales Research Ethics Committee 3 (Ref 24/WA/0181), and regulatory permission by the Medicines and Healthcare Products Regulatory Agency (CTA reference 21323/0063/001-0004). NHS permission has been granted by the Health Research Authority (HRA) and capacity and capability confirmed by each individual NHS organisation. The study is registered on ISRCTN (ISRCTN14019493 https://doi.org/10.1186/ISRCTN14019493) and on the NIHR portfolio (CPMS 55712). Cardiff University is the sponsor ([contact]) and was not involved in the preparation of this manuscript or the decision to submit. Personal data is held with the explicit consent of participants, independently of study data. We shall disseminate our findings via national and international peer-reviewed journals and conferences. Oversight of the study is being performed by an IDMC (comprising two expert paediatricians and an expert statistician) and an independent TSC (comprising three expert paediatricians, an expert statistician and two lay representatives). Appointments to these committees were made with the approval of the NIHR and a meeting is being held at least annually.

## Discussion

Infants born preterm at ≤29+6 weeks’ gestation are at risk of lung disease in the early neonatal period and subsequently vulnerable to LRTIs during infancy and childhood. These LRTIs may lead to increased healthcare utilisation with visits to GPs, A&E and hospital admissions with time missed from work for the parents. In addition, the LRTIs may exacerbate the existing lung disease. Therefore, it is important to aim to prevent viral infections in infancy. Currently, preventative strategies are largely limited to anti-RSV antibody prophylaxis, maternal RSV immunisation during pregnancy and avoidance of viral infections especially in nurseries. TIBVs, such as Bactek, are increasingly used and provide a promising therapeutic avenue for preterm-born infants to target postdischarge respiratory viral infection in this vulnerable group of preterm-born infants.

We opted to study the preterm-born group below 30 weeks’ gestation at birth as this is the group at the highest risk of developing the important lung disease BPD in the neonatal period, which can have lifelong consequences and thus is an important group for intervention to prevent LRTIs after discharge from the neonatal unit. If this treatment is successful in decreasing LRTIs during the first year of life, there should be large cost savings for the health services throughout the world. The cost to the health service for each hospital admission for a chest infection is over £6000 (in 2012).^22^ Importantly, it will also benefit the parents and their infants. The definition of an LRTI may, in some cases, be difficult to discriminate from an upper RTI. However, any potential LRTI will be verified by research staff at the sites, so this should ensure that the primary outcome is accurate. We have also included the effects of LRTIs on the parents, including time off nurseries and off work. The results should be easily interpretable as we are adequately powered to meet the objectives of the study and will ensure adequate data are collected.

Throughout the development of the study, we have engaged parents who have been through the medical care of preterm-born babies at the extremes of prematurity, including those with BPD. Importantly, by surveying a significant number of parents in different UK neonatal centres, we were made aware of outcomes including LRTIs after discharge and long-term consequences of preterm delivery. We believe that with their input, we have developed an important study to address their important concerns of preventing hospitalisation and possibly long-term respiratory consequences of prematurity.
